### *Gradation of adverse reactions*

Grade 1: mild adverse event: refers to the effects that may happen due to the compound that are temporal and don't cause permanent harm or incapacity.

Grade 2: moderate adverse event; refers to the effects that may happen due to the compound that are temporal but require support from other therapeutics to be corrected and don't cause permanent harm or incapacity.

Grade 3: severe adverse event; refers to the effects that may happen due to the compound that might be temporal or permanent, without risk of mortality or incapacity.

Grade 4: adverse advent with risk of death or incapacity.

Evaluated through the following study:

Electrocardiogram: QT interval prolongation.

Blood count: bone medulla suppression, defined with the following values: neutrophiles < 500/microliters, platelets < 20,000/microliter, reticulocytes < 20,000 / microliter.

Hepatic failure: INR > 1.4, ALT > 33 units/liter, AST > 55 units/liter, total bilirubin > 4 mg/dl, platelets < 150,000/microliter.

Due to the nature of the study, having a captive population that comes to the INER at least five days a week, it is possible to estimate the number of days to the outcome. All participants will be instructed to notify the researchers in case of presenting cough, dyspnea or any other new sign or symptom. Weekly researchers will ask all included subjects about the symptoms associated with COVID-19, as well as any possible adverse events.

If any study subject presents adverse reactions, the treatment will begin immediately, and it will be notified at the same time. The initial treatment will be administered at the INER, support from other institutions will be requested, if necessary, without cost for the subject.

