### *Secondary outcomes*

1. Admission to the Intensive Respiratory Care Unit , need of invasive/non-invasive mechanical ventilation, death secondary to COVID-19, proved via PCR-TR according to the OMS protocol.
2. Incidence and severity of adverse events  
Adverse event: all medical events in the subjects included in the trial. The adverse event doesn't necessarily need to have a causal relation with the studied treatment. Examples of adverse events include abnormal symptoms and signs, hypersensitivity reactions or alterations in laboratory samples.  
Severe adverse event: defined as an event that results in the subject's death, in an event that threatens life, that requires hospital admission or causes incapacity.  
Due to the known effects of HCQ, special attention will be given to the incidence of the following adverse events:
  - a) Cutaneous reaction, generally when used along other drugs.
  - b) Medullar suppression, which must be watched over monthly through a control blood count.
  - c) Severe hypoglycemia, in which case the treatment must be suspended.
  - d) Proximal myopathy with proximal weakness or muscular atrophy.
  - e) Increase of suicidal risk according to the C-SSRS scale.

Adverse reactions are defined as the answer to a compound that is harmful and involuntary, that occurs at doses that normally are administrated to human beings. The described adverse reactions are:

- 1- 10% ophthalmologic, dose dependent.
- 2- Non-defined frequency: dermatologic, endocrine, metabolic, gastrointestinal, hematologic, hepatic, central nervous system, immunologic.

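### Grade 3 ('severe') has no lower bound other than its label, so the Grade 3 adverse-event count depends on assessor discretion

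*Protocol*

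**What the plan says.** Protocol, Secondary outcomes, item 2 is "Incidence and severity of adverse events". The general grading for it stands under Gradation of adverse reactions:

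- Grade 1, labelled mild: effects "that are temporal and don't cause permanent harm or incapacity".
- Grade 2, labelled moderate: effects "that are temporal but require support from other therapeutics to be corrected and don't cause permanent harm or incapacity".
- Grade 3, labelled severe: "Grade 3: severe adverse event; refers to the effects that may happen due to the compound that might be temporal or permanent, without risk of", the excluded risks being death and incapacity.
- Grade 4, with no severity label: "Grade 4: adverse advent with risk of death or incapacity".

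No sentence says which grade to assign when an event fits more than one. The ECG and laboratory items that follow define abnormalities but assign none of them to a grade, and no external toxicity scale is cited. Separately, Secondary outcomes uses the term severe adverse event for something else, "defined as an event that results in the subject's death, in an event that threatens life, that requires hospital admission or causes incapacity".

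**The concern.** A severity grade is useful only if two assessors with the same facts reach the same grade. The Grade 3 clause sets a ceiling (no risk of death or incapacity) but no floor. It mentions neither intensity nor need for treatment nor hospital admission, and it admits temporary and permanent effects alike. The temporary, risk-free events that Grades 1 and 2 describe therefore also fit it.

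What is at stake is the Grade 3 count in each arm. Grades are assigned when events are recorded, so inconsistent assignment may not be recoverable at analysis. The monitoring committee is to watch toxicity (Data and security monitoring committee), and Ethical considerations expects more adverse events on hydroxychloroquine. A count of severe events should not turn on private conventions.

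**Working it through.** No figure in the protocol bears on this point, so there is none to reproduce. The check is logical, and its inputs are the four grade clauses.

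**Step 1. Conditions set by each clause, labels left aside.**
- Grade 1: temporary, no permanent harm, no incapacity caused.
- Grade 2: the Grade 1 conditions, plus other therapy needed.
- Grade 3: temporary or permanent, no risk of death, no risk of incapacity.
- Grade 4: risk of death or of incapacity.

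**Step 2. Grades met by each kind of event.** The last column gives the charitable reading, in which the contrast drawn in Grade 2 implies that Grade 1 events need no other therapy. Risk means risk of death or incapacity.

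| Event | Clauses as written | Grade 1 read as untreated only |
|---|---|---|
| Temporary, no therapy, no risk | 1, 3 | 1, 3 |
| Temporary, therapy needed, no risk | 1, 2, 3 | 2, 3 |
| Permanent, no risk | 3 | 3 |
| Temporary, no therapy, risk but no incapacity caused | 1, 4 | 1, 4 |
| Temporary, therapy needed, risk but no incapacity caused | 1, 2, 4 | 2, 4 |
| Permanent with risk, or incapacity caused | 4 | 4 |

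**Step 3. What is left for Grade 3.** On the charitable reading, Grades 1 and 2 together already cover every temporary event without permanent harm or incapacity. Grade 3 excludes risk of incapacity, so no temporary event belongs to Grade 3 alone. Only the word severe can move a temporary event there.

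**Step 4. Completeness.** Assume that each event is either temporary or permanent, that a temporary event leaves no permanent harm, and that causing incapacity implies a risk of it. The possible kinds of event are duration (2) × therapy needed (2) × risk of death (2) × hospital admission (2) × incapacity (3: no risk, risk only, caused) = 48. Those meeting more than one grade are the temporary ones that cause no incapacity: 1 × 2 × 2 × 2 × 2 = 16. Of these, 4 carry no risk and overlap with Grade 3, and 12 carry risk and overlap with Grade 4. The other 32 meet one grade: 4 meet Grade 3 and 28 meet Grade 4. No kind of event meets Grade 1 alone or Grade 2 alone. The total of 16 is the same on both readings.

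**Step 5. Would a tie-break alone repair it?**
- Highest grade met, on either reading: Grade 4 takes 12 + 28 = 40 and Grade 3 takes 4 + 4 = 8. Grades 1 and 2 are empty.
- Lowest grade met, clauses as written: 16, 0, 4 and 28 for Grades 1 to 4. Grade 2 is empty.
- Lowest grade met, charitable reading: 8, 8, 4 and 28. All four grades are used, but Grade 3 holds permanent effects only, and the 12 transient kinds that carry risk fall into Grades 1 and 2.

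These are counts of logical kinds, not expected event frequencies. They show that the definitions themselves need to change.

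**The case against.** The strongest reply is that each of the first three grades carries a severity word, and that the check above sets those words aside. Read as an ordered scale, a brief untreated nausea is mild, and no sensible assessor would call it severe. Nor would one call a transient life-threatening event mild. The contrast in Grade 2 also largely separates it from Grade 1. This stands in part: the intended order is clear, and a reader should not infer that every transient event is graded severe, or that the whole scale is nested. Grades 3 and 4 exclude each other. What the labels do not supply is a boundary: when a temporary event is severe rather than mild or moderate is left to the bare word.

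A reader might also infer that the severity outcome has no value at all, or that real toxicity would be hidden. The documents do not support that. Secondary outcomes defines a severe adverse event by its consequences, which gives a count by arm without any grade. It also lists events of special attention. Gradation of adverse reactions gives numerical limits for marrow suppression and hepatic failure and names QT prolongation. All of these can be reported whatever the grade. The third specific objective concerns the risk of adverse effects, and Statistical analysis describes no comparison by grade.

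Translation may explain some of the wording, and a statistical analysis plan that is not shown could add a tie-break. Neither removes the point, because the faulty definitions are in the protocol and Step 5 shows that a tie-break alone does not mend them.

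**Conclusion.** The point holds in a limited form. The Grade 3 clause has no lower bound beyond its label, so temporary events without risk of death or incapacity can be put in Grade 1 or 2 or in Grade 3 at discretion. A transient event with such risk can meet Grade 1 and Grade 4. The Grade 3 count under the severity outcome is therefore not reproducible.

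No numerical size can be given: the protocol states no expected adverse-event frequencies or severity mix, and any assumed split would only return its own assumption. The conclusion rests on the wording of the four clauses and on the absence of an assignment rule. Overall adverse-event incidence, the consequence-based severe-event count, the listed events and the primary outcome are untouched. Blinding limits bias between the arms but does not give the grade a fixed meaning.

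**What to change.** Make the grades mutually exclusive and state that the highest grade met is assigned.

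- Grade 1: temporary, no other therapeutics needed, no permanent harm, no risk of death or incapacity.
- Grade 2: as Grade 1, but other therapeutics needed.
- Grade 3: an explicit lower bound that Grades 1 and 2 do not meet, for example permanent harm without incapacity. If a severe temporary category is wanted, define it by a stated criterion.
- Grade 4: unchanged.

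With permanent harm as the Grade 3 bound, and keeping its exclusion of risk of death or incapacity, the 48 kinds of event divide as 2 + 2 + 4 + 40, one grade each. The highest-grade rule becomes necessary once a temporary Grade 3 criterion is added.

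Also reconcile the scale with Secondary outcomes. The term severe adverse event now names both Grade 3, which excludes risk of death, and a category that includes death. Hospital admission appears only in the second, and its place in the grades should be stated.

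The cost is minor rewording of the protocol and case report form, with no new visits or subjects. Fewer events may be labelled severe than under a loose reading of the present text.

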#### *Ending of recruitment*

#### *Tests to perform*

- Minimum tests at recruitment (before randomization) and at 30 and 60 days:
  - Blood count
  - Serum electrolytes
  - Blood chemistry (3 elements): to quantify the effects on blood sugar and rule out type 2 diabetes mellitus at baseline.
  - Hepatic profile
  - Electrocardiogram: to evaluate the incidence of heart conduction alterations.
- 10-respiratory virus and SARS-CoV-2 panel, only in case of symptoms.

At 30 and 60 days: surveillance of adverse events.

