### *Final calculation*

According to the proposed statistical analysis, the difference in time to outcome will be performed with a log-rank test, using the following formulas:

$$n = \frac{d}{2 - S1(\infty) - S2(\infty)} \text{ y } d = (Z\alpha(2) - Z1 - \beta)^2$$

Considering a difference of 10% of higher survival rates free of COVID-19 and considering a reported survival rate free of COVID-19 of 76%, a sample size of 159 per group is obtained. Considering the losses, it is decided that 200 subjects will be included per group, for a total of 400 subjects.

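### Marrow suppression is defined only by very low blood-count limits, so its reported incidence would be weak evidence that hydroxychloroquine leaves neutrophils and platelets unaffected.

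*Protocol*

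**What the plan says.** Under Secondary outcomes, the protocol makes the incidence and severity of adverse events a secondary outcome. It adds that, because of the known effects of the drug, "special attention will be given to the incidence of the following adverse events". One item on that list is "Medullar suppression, which must be watched over monthly through a control blood count".

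The section on gradation of adverse reactions supplies the only numeric definition: "bone medulla suppression, defined with the following values: neutrophiles < 500/microliters, platelets < 20,000/microliter, reticulocytes < 20,000 / microliter". It does not say whether one of these limits is enough or all three are needed. The same section has a four-step severity scale that begins with "Grade 1: mild adverse event: refers to the effects that may happen due to the compound that are temporal", but no step carries a blood-count value. Its hepatic failure line ends with "total bilirubin > 4 mg/dl, platelets < 150,000/microliter", so a second platelet limit appears there for a different event.

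Two other statements bear on the point. The general definition of an adverse event is wide: "Examples of adverse events include abnormal symptoms and signs, hypersensitivity reactions or alterations in laboratory samples". Blood counts are scheduled under "Minimum tests at recruitment (before randomization) and at 30 and 60 days". On size, "it is decided that 200 subjects will be included per group, for a total of 400 subjects".

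**The concern.** An event singled out for attention should have a definition that can register the effect being watched for. Here a worker whose neutrophils fell from 4,000 to 700, or whose platelets fell from 250,000 to 30,000, would not meet the neutrophil or platelet limit for marrow suppression. The platelet count of 30,000 would meet the platelet criterion listed under hepatic failure instead.

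A count of zero or near zero in both arms is therefore likely for these two cell lines, whether or not the drug lowers counts. It could easily be read as evidence of haematological safety. That matters for a prophylactic drug: the Experimental group section foresees that, depending on interim results, both groups may be given it.

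**Working it through.** The protocol states no expected rate for this event, so there is no figure of its own to reproduce.

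**Inputs from the protocol.** Limits of 500 neutrophils, 20,000 platelets and 20,000 reticulocytes per microliter; 200 subjects per arm; two-sided 5% level; counts at baseline, day 30 and day 60.

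**Assumed inputs.** Baseline counts are log-normal, with 95% of workers between 1,800 and 7,500 (neutrophils) and between 150,000 and 400,000 (platelets). The drug lowers every worker's count by the same proportion f.

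**Step 1: spread and centre.** σ = (ln upper − ln lower)/(2 × 1.96).
- Neutrophils: σ = 0.364, median √(1,800 × 7,500) = 3,674. Reaching 500 from the median needs a fall of 1 − 500/3,674 = 86%.
- Platelets: σ = 0.250, median √(150,000 × 400,000) = 244,949. Reaching 20,000 needs a fall of 1 − 20,000/244,949 = 92%.

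**Step 2: expected cases per 200 at one blood draw.** P = Φ[(ln limit − ln median − ln(1 − f))/σ].

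| Fall f | Neutrophils <500: P | × 200 | Platelets <20,000: × 200 |
|---|---|---|---|
| 0 | 2.1e-8 | 4e-6 | 1e-21 |
| 20% | 5.7e-7 | 0.0001 | 7e-18 |
| 50% | 1.8e-4 | 0.035 | 4e-11 |
| 60% | 1.5e-3 | 0.31 | 2e-8 |

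For the 50% row: neutrophils (6.215 − 8.209 + 0.693)/0.364 = −3.57; platelets (9.903 − 12.409 + 0.693)/0.250 = −7.24. Having two draws after baseline can at most double these figures.

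**Step 3: sensitivity to the assumed distribution.** With log-normal neutrophils of mean 3,500–4,000 and SD 1,200–1,500, the expected number per 200 after halving runs from 0.0005 to 0.44. At the least favourable end (mean 3,500, SD 1,500) the chance of no case at all is still 64%. After a 30% fall the chance of no case is at least 97.5% throughout this range.

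**Step 4: reticulocytes.** This limit behaves differently. With an assumed SD of 20,000, expected cases per 200 are:
- mean 60,000: 0.13 with no fall, 1.1 after 20%, 3.4 after 30%;
- mean 50,000: 2.9 with no fall, 10.8 after 20%, 20.8 after 30%.

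If any one limit suffices, the event can occur, and on the second assumption it can occur without any drug effect. If all three are required, the neutrophil and platelet limits decide, and the event is close to unreachable under a uniform fall. The list of tests names a blood count but does not mention reticulocytes.

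**Step 5: what the same draws could show.** For log counts, the standard error of the difference between arms is σ√(1 − r²)√(2/200), where r is the assumed correlation with baseline. A 10% fall is a difference of −ln 0.9 = 0.105. For neutrophils with r = 0 the standard error is 0.0364, so power = Φ(0.105/0.0364 − 1.96) = Φ(0.93) = 82%. With r = 0.5 it is 92%, and with r = 0.7 it is 98%. For a 20% fall it exceeds 99%. A comparison of raw means under the Step 3 distributions gives 65–92% for a 10% fall with 200 per arm, and 55–84% if only 159 per arm contribute.

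**Step 6: if toxicity is rare rather than uniform.** Zero cases in 200 excludes only true rates above 1 − 0.05^(1/200) = 1.5% (one-sided 95%). The chance of seeing none is 0.99^200 = 13% at a true rate of 1%, and 37% at 0.5%. Against 0/200 on placebo, six cases are needed for Fisher p < 0.05 (6 v 0 gives 0.030; 5 v 0 gives 0.061). Power is 2% at a true rate of 1% and 21% at 2%.

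**The case against.** The strongest reply is that the trial is not blind to lower counts. A reader might infer that only the crossing of these limits is recorded, or that the trial is bound to report no marrow effect. The documents do not support either reading. The adverse-event definition expressly includes laboratory alterations, so a fall to 700 neutrophils can be recorded. The severity steps are generic and not tied to the marrow limits, so such an event could be graded as mild or moderate. This stands. The shortfall is one of label and threshold: that route has no numeric limit, so recording depends on judgement, and the event would not count towards the one singled out.

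The reticulocyte limit also defeats any claim that all three limits are unreachable. That too stands, so the numerical argument is confined to neutrophils and platelets, or to the all-three reading.

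A uniform proportional fall is only one model. If the drug caused a severe fall in a few workers, the present limits would catch those workers and a comparison of mean log counts would mostly miss them. This is a good reason to keep the limits. It does not make a zero count reassuring, because 200 per arm has little power for rare events. It is also fair that a 10% shift, which leaves most workers within the assumed range, is not marrow suppression in any clinical sense; the model answers the different question of whether counts move.

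The protocol does not require the workers to be healthy: it asks for no respiratory symptoms and sets no blood-count criterion. Finally, models and tables usually belong in a statistical analysis plan, which is not at hand. The definition itself, however, is fixed in the protocol, and a plan that follows it would inherit the problem.

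**Conclusion.** The point holds in a limited form. The protocol's only definition of a named safety event would register almost no neutrophil or platelet cases even if those counts were halved: about 0.04 and under 1e-9 expected per 200 on the stated ranges, and up to 0.44 for neutrophils under the widest alternative tried. All of these rest on assumed distributions and a uniform fall, since the protocol gives no counts or rates. The definition also leaves the one-or-all rule open and sits beside a platelet limit 7.5 times as high (150,000/20,000) under another heading.

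The reported incidence of marrow suppression would therefore be weak evidence of haematological safety. It does not follow that falls in counts would go unrecorded or that the result must be zero in both arms. The issue concerns a secondary safety outcome and leaves the primary comparison untouched.

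**What to change.** In the section on gradation of adverse reactions, keep the present limits as the most severe reporting category and state whether one or all three must be met. The authors should also reconcile the platelet limit given for marrow suppression with the one given under hepatic failure; which value is right is theirs to settle.

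In the Statistical analysis section, add a between-arm comparison of log neutrophil and log platelet counts at day 30 and day 60, adjusted for the pre-randomisation value, with a table of shifts from baseline by arm. State that absence of a marrow effect will not be concluded from the number of workers below the present limits.

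The cost is some wording, one extra model and one table, using blood counts already scheduled. It needs no new test or visit and adds no dosing or stopping rule.

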#### *Exclusion criteria*

- Known hypersensitivity to HCQ, evidenced by anaphylaxis.
- Current treatment with HCQ or chloroquine.
- Weight less than 50 kg at the basal evaluation.
- Women with last menstrual date a month before recruitment without a pregnancy test.
- Women with positive pregnancy test.
- Lactating women.
- History of chronic hepatic disease (Child-Pugh B or C)
- History of chronic kidney disease (GFR lower or equal to 30)
- History of treatment with tamoxifen.
- History of retinopathy of any cause, and/or loss of central vision, loss of nocturnal visual acuity, blurred vision and alteration of color vision.

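### The hepatic failure definition lists five laboratory cut-offs with no combination rule and no reference to baseline, so the count by arm depends on how the list is read

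*Protocol*

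**What the plan says.** Under Gradation of adverse reactions, the protocol gives laboratory rules for reading the safety tests. The liver rule is "Hepatic failure: INR > 1.4, ALT > 33 units/liter, AST > 55 units/liter, total bilirubin > 4 mg/dl, platelets < 150,000/microliter". The values are separated by commas, with no word for any, all or a minimum number. No change from baseline, repeat test or clinical sign is required. The marrow-suppression rule just above it has the same form and ends "platelets < 20,000/microliter, reticulocytes < 20,000 / microliter".

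Three other sections bear on how the rule works:

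- **Tests to perform** sets "Minimum tests at recruitment (before randomization) and at 30 and 60 days". The list includes a blood count and "Hepatic profile"; INR is not named.
- **Exclusion criteria** has one liver item, "History of chronic hepatic disease (Child-Pugh B or C". No entry limit is set on ALT, AST, bilirubin, INR or platelets.
- **Secondary outcomes** lists "Incidence and severity of adverse events". Laboratory alterations are given as examples of adverse events, and "The adverse event doesn't necessarily need to have a causal relation with the studied treatment".

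Estimating the risk of adverse effects in each arm is also one of the Specific objectives.

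**The concern.** The protocol has chosen to fix numerical cut-offs for a named safety event, but they cannot be applied without a further decision. Two analysts following the text could report very different hepatic failure rates from the same data.

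Neither plain reading serves the safety objective well. If any one value is enough, small isolated deviations carry the label. A platelet count of 149,000 becomes hepatic failure, although the same section puts platelet-defined marrow suppression below 20,000. Crossings unrelated to treatment occur in both arms and dilute a real difference. If all five values are needed, a worker with clear liver injury who misses one cut-off is not counted under the label.

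The definition also takes no account of the pre-randomisation value, so it does not separate a new abnormality from one present at entry. The reported rate, the comparison by arm and the toxicity information seen by the monitoring committee could all be affected.

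**Working it through.** The protocol states no expected rate for this event, so there is no figure of its own to reproduce. The check applies each reading in turn.

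**Inputs from the protocol.** Five cut-offs (Gradation of adverse reactions); baseline and two later test days, 30 and 60 (Tests to perform); 200 per arm (Final calculation).

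**Inputs assumed, not in the protocol.** ALT geometric mean 16 to 24 U/L, between-person log-SD 0.40, within-person CV 10% to 25%; AST geometric mean 21 U/L; platelets mean 255,000, SD 55,000. ALT and AST are correlated, each worker keeps a personal level across visits, and all tests are done. There is no drug effect. INR and bilirubin are left out, so they add nothing to the count.

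**1. Any-of reading.** A worker is a new case if ALT > 33, AST > 55 or platelets < 150,000 on day 30 or day 60, with none of these at baseline. With 400,000 simulated workers per scenario, the percentage of baseline-clear workers who become cases is:

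| ALT geometric mean | CV 10% | CV 20% | CV 25% |
|---|---|---|---|
| 16 | 3.5 | 6.2 | 7.9 |
| 20 | 6.1 | 11.5 | 14.3 |
| 24 | 9.5 | 17.6 | 21.7 |

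A rerun with AST log-SD 0.25, ALT/AST correlation 0.6 and platelet within-person CV 8% gave 3.4% to 21.3%, with 11.4% in the central cell.

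The denominator matters. In the central case (mean 20, CV 20%), 11.5% is the rate among workers clear at baseline. As a share of all randomised it is 9.7%, and 0.097 × 200 = 19 per arm. Because the definition ignores baseline, workers already beyond a cut-off also count; the share with any post-baseline crossing is then 21.9%, or 0.219 × 200 = 44 per arm.

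**2. Cruder cross-check.** Suppose each of three cut-offs is crossed by a share p of healthy values, independently over two visits. The chance of at least one crossing is 1 − (1 − p)^6:

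- p = 1%: 5.9%
- p = 2.5%: 14.1%
- p = 5%: 26.5%

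Correlation within a person would lower these. The order of magnitude agrees, and the result clearly depends on the assumed tail.

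**3. Dilution, as an illustration only.** Take an invented true liver effect of 0.5% v 5.5% (ratio 11). With 200 per arm and a two-sided 5% test:

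- SE = √(0.005 × 0.995/200 + 0.055 × 0.945/200) = 0.0169
- 0.050/0.0169 − 1.96 = 1.00, so power is 0.84

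Add a 10% background of chance crossings:

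- 0.10 + 0.90 × 0.005 = 10.5% (10.45% unrounded)
- 0.10 + 0.90 × 0.055 = 15.0% (14.95% unrounded)
- The ratio falls to 1.4
- SE = √(0.1045 × 0.8955/200 + 0.1495 × 0.8505/200) = 0.0332
- 0.045/0.0332 − 1.96 = −0.60, so power is 0.27

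**4. All-of reading.** A worker with INR 2.5, bilirubin 8 mg/dl, ALT 900 and platelets 180,000 does not meet the rule, because platelets are not below 150,000. False positives essentially vanish: five independent 2.5% tails give 0.025^5, about 1 in 100 million. If the hepatic profile does not include INR, no worker can meet the rule.

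**The case against.** The strongest reply is that this is a label within a secondary safety outcome. Hepatic failure is not among the five adverse events singled out for special attention. No stopping rule, sample size or named comparison is tied to it. Change-from-baseline rules and separate tabulation of analytes are commonly left to a statistical analysis plan, and one may exist. That limits the weight of the point. It does not remove it: a composite whose cut-offs the protocol fixes should also say how they combine.

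Three stronger readings are tempting, and the document does not support them.

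- **That 3% to 22% of these workers will be labelled.** The protocol gives no distribution for any of these values. The range follows from the assumptions above and moves with them. The 0.5% v 5.5% effect is likewise invented, and dilution bites only if the any-of label is the sole hepatic analysis, which the protocol does not say.
- **That under all-of, true liver failure goes unseen.** Secondary outcomes counts laboratory alterations as adverse events without requiring a causal link, and counts life-threatening events or hospital admission as severe. The worker in step 4 would be recorded; only the label would be missing.
- **That the label should become INR together with bilirubin, or that abnormalities should count only in workers normal at entry.** The first rests on a test the protocol does not name and is again a conjunction that healthy staff would seldom meet. The second would hide a worker whose ALT rises from 40 to 400. In the central case 0.097/0.115 = 84% are clear at baseline, so about 16%, or 31 per arm, could drop out of at least one count. The Statistical analysis section says that every randomised subject is analysed.

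**Conclusion.** The point holds as a defect in a stated definition. The list has no combination rule and no baseline reference, and its two plain readings give very different counts of the same safety event. That conclusion needs no outside figure.

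The size of the any-of problem is conditional: about 3% to 22% of workers clear at baseline, centrally about 10% of all randomised or 19 per arm, under the assumed ALT, AST and platelet distributions with no drug effect and complete testing. Under all-of, the consequence is a missing label, not a missing event, and the rule becomes impossible to meet if INR is not measured.

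The point concerns a secondary safety outcome and leaves the primary comparison untouched. It is worth correcting because the correction is mostly wording and the label is a serious one to report in healthy staff.

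**What to change.** - Tabulate the laboratory values by arm as separate abnormalities relative to each worker's own baseline, as new or worsened. Keep workers who are abnormal at baseline in the tabulation so that worsening is seen.
- Do not call an isolated crossing of one cut-off hepatic failure.
- State the combination rule for any composite hepatic label, and likewise for the marrow-suppression list.
- Reconcile the list with Tests to perform: say whether the hepatic profile includes INR, or how a definition that uses INR is to be assessed without it.

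The clinical definition of hepatic failure and its cut-offs are for the investigators to set; none is proposed here.

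The cost is a change of wording and slightly more tabulation, using the baseline, day-30 and day-60 tests already planned. INR is the exception: if it is not part of the profile and is to be kept in the definition, a test must be added. Small isolated rises would no longer carry the failure label, but they would stay visible as laboratory abnormalities.
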